### 8.3.4 Follow-up

Follow-up investigation includes recovery of renal function, patients' mortality. When patient's condition is improved and CRRT is not necessary, patient is followed whether he or she is on dialysis at discharge, and renal recovery is sought at 1st outpatient department visit after discharge. Also, mortality at discharge and 28 days after initiation of CRRT is investigated. Follow-up investigation is conducted according to patient's outpatient department visit schedule and no extra-visit for the study is planned.

## 9. Precautions using study medication

### 9.1 Precaution considering the study medication: SK chemicals corp. 'IV futhan'

#### 1. Warning

The patient should be inspected thoroughly to reveal any history of hypersensitivity, because of the concerns for shock or anaphylactoid reaction. Also, in case of a shock, prepare for emergency treatment, observe, and if these symptoms occur, immediately stop administering the medication and treat properly.

#### 2. Prohibited in following patients

The patients who have history of hypersensitivity by the medication

#### 3. Adverse events

##### (1) Improvement of acute symptom in pancreatitis

117 (1.74%) out of 6,732 cases showed adverse events. The symptoms included 55 cases (0.82%) of liver function abnormalities including GOT/GPT elevation, 23 cases (0.34%) of hypersensitivity reactions such as rash, urticaria, and 14 cases (0.31%) of electrolyte imbalance such as hyperkalemia. (Re-examination conclusion report result in Japan)

##### (2) DIC

241 (6.69%) out of 3,602 cases showed adverse events. The major symptoms included 185 cases (5.14%) of electrolyte imbalance such as hyperkalemia and hyponatremia, 53 cases (1.47%) of liver function abnormalities, and 11 cases (0.31%) of hypersensitivity reaction. (Re-examination conclusion report result in Japan)

##### (3) Anticoagulation of extracorporeal circuit in patients with hemorrhagic tendency

48 (1.18%) out of 4,053 cases showed adverse events. The major symptoms included 41 cases (1.01%) of gastrointestinal symptom, and 9 cases (0.22%) of hypersensitivity reaction. (Re-examination conclusion report result in Japan)

##### (4) Severe adverse events

###### ① Shock, anaphylactoid reaction

Detailed observation is required due to possibility of shock and anaphylactoid reaction (respiratory distress, asthma-like reaction). And if these symptoms appear, immediate discontinuation of medication with proper management is required.

###### ② Hyperkalemia

(Pancreatitis: 0.19%, DIC: 4.53%, anticoagulation for extracorporeal circuit: 0.02%; Re-examination conclusion report result in Japan)

Extra caution is required due to possibility of hyperkalemia, when using potassium sparing diuretics, potassium containing medication. When it occurs, immediate

discontinuation of the medication and proper management should follow. Also, there have been some cases of arrhythmia due to hyperkalemia.

(5) Other adverse events

- ① Skin: Occasionally rash, rarely erythema, urticaria occurred, and the medication is discontinued after the symptom appears.
- ② Musculoskeletal: Myalgia and arthralgia have been reported.
- ③ Gastrointestinal: Anorexia, diarrhea, nausea, vomiting have been reported.
- ④ Hepatobiliary: Occasionally GOT/GPT elevation, ALP elevation, LDH elevation, total bilirubin elevation and Jaundice have occurred.
- ⑤ Hematologic: Occasionally leucopenia, eosinophilia, thrombocytopenia, and thrombocytosis have occurred. Bleeding tendency can occur, and in this occasion, medication dose will be tapered or discontinued.
- ⑥ Cardiovascular: Palpitation, hypertension and hypotension can occurred.
- ⑦ Urologic: Intermittently BUN/Creatinine elevation occurred.
- ⑧ Systemic: Headache, chest pain, general weakness, chest discomfort, and rarely fever have been reported.
- ⑨ Administration site: Rarely pain and angiitis with swelling occurred.

4. General precaution

- (1) Hyperkalemia and hyponatremia due to potassium excretion inhibition and sodium excretion acceleration can be occurred. Hence serum potassium and sodium level should be checked regularly and if any abnormalities have been observed, immediate discontinuation and proper management should be performed.
- (2) When using Potassium containing medication and potassium sparing diuretics in combination, be cautious about hyperkalemia. Also, when abnormal serum potassium level is confirmed, electrocardiography should be checked to identify arrhythmia. When used in extracorporeal circuit, this medication can aggravate hemorrhage. Hence close observation is required, and if needed, the medication should be tapered or discontinued

5. Administration to elderly

Elderly are generally with reduced physiologic function and careful caution for dose reduction is required.

6. Administration to pregnant or lactating female

- (1) Since safety in administration during pregnancy has not been confirmed, medication to pregnant female or female who is possible to have pregnant should be considered when

the benefit of the treatment exceeds the risk. In animal study, there has been reports of increase in fetal mortality (rat, rabbit), inhibition in fetal weight gain (rat), and decrease in delivery rate (rat)

- (2) In animal study (rat), there has been report of transition of metabolites via breast milk, thus when drug is administered, breast feeding should be stopped.

## 7. Administration to child

### (1) Precaution during prescription

- ① The medication should be used after completely dissolved by 5% glucose fluid.
- ② When dissolving the medication, needle should be inserted in the middle of the rubber of the vial. Also, if 19 gauge or thicker needle is used, the rubber topping or part of it can drop into the vial. Hence, precaution is required.
- ③ Normal saline or fluid containing mineral should not be directly injected to the vial due to the risk for crystal formation.

### (2) Precaution after prescription

The medication is administered as soon as possible.

### (3) Precaution during injection

- ① Dosage: When the medication is administered to extracorporeal circuit, appropriate dosage is required with consideration to bleeding tendency, residual blood in extracorporeal circuit, and thrombokinesis or blood coagulation time.
- ② Infusion rate: The medication should not be administered into vein or extracorporeal circuit rapidly.
- ③ Dialyzer: The medication is highly absorbable to AN69 (polyacrylonitrile) membrane, hence it is prohibited to be used with the membrane.
- ④ Injection: Extravasation of the medication can lead to inflammation and necrosis of the injection site, hence it is crucial not to extravasate the medication.

## 10. Study discontinuation, drop out, or analysis exclusion criteria

## 10.1 Study discontinuation and drop out criteria

All patients who enrolled in the study should be recorded of the completion of the study, and if the medication is discontinued or observation is stopped, the reason is recorded. The criteria for patient's drop-out are as follows.

- ① Circumstance that violates inclusion/exclusion criteria
- ② Serious adverse events occurred in patients or patients demands to be dropped out of the study due to adverse events.
- ③ Patient or legal guardian demand the discontinuation of the study due to unsatisfactory curative value during the study.
- ④ Severe hemorrhage
- ⑤ Critical violation of study protocol by principal investigator, researcher or patients.
- ⑥ Patients or legal guardian's withdrawal of the consent.
- ⑦ When patients cannot be followed.
- ⑧ When the patient takes a medication that can influence the study result, without the researcher's authorization during study period.
- ⑨ When the patient is decided not fit for the study progression by researchers.

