### 6.3 Target number of subjects and its estimation basis

#### 6.3.1 Number of subjects

We are planning to enroll 33 subjects per group that is suitable for inclusion/exclusion criteria and analyze final group of 31 subjects.

|                                                      | Futhan group | No-anticoagulation group | Total subjects |
|------------------------------------------------------|--------------|--------------------------|----------------|
| Validity assessment subjects                         | 31           | 31                       | 62             |
| Validity assessment subjects including drop-out (5%) | 33           | 33                       | 66             |

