## 10.2 Disposal of violation on protocol and non-compliance

The principal investigator and researchers should fully recognize and perform the study protocol, hence the protocol is not violated. However, the inevitable violation will be dealt with as follows.

In case of severe protocol violation, researcher should disregard the patient's data from the analysis and the criteria are as follows.

- ① Failure to acquire written consent
- ② Violation of inclusion/exclusion criteria
- ③ Administration of the medication that is prohibited to use in combination during the study.

Other violation of protocol that is decided to be minor and is not thought to influence the study analysis is thoroughly documented with the degree of violation, reason. Afterwards, the violation is evaluated by researcher, funder, monitor, statistician whether the violation has tempered with the study and included in the PP analysis.

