### 11.3 Analysis method

#### 11.3.1 General principal of result analysis

The data retrieved from the patients during the study is analyzed by Safety analysis, ITT (Intent-To-Treat) analysis and PP (Per Protocol) analysis.

The Safety analysis is analysis including all data from patients in futhan group who have taken the medication at least once and no-anticoagulation group

The ITT analysis is analysis including all data from patients who have been confirmed whether he or she is dead or alive in futhan group who have taken the medication at least once and no-anticoagulation group. And when there is a missing value or patient drop out before the study is over, the latest value can be analyzed as data acquired at relevant time (Last Observation Carried Forward Method).

The PP analysis is analysis including the data from patients who have successfully concluded the study protocol.

The data regarding validity is principally analyzed by PP analysis, and additionally analyzed by ITT analysis.

The data regarding safety is principally analyzed by Safety analysis.

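### Serious adverse events and severe hemorrhage are drop-out criteria and the principal ICU-mortality analysis is per protocol, so patients with these events may be removed from the primary result

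*Protocol*

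**What the plan says.** The primary endpoint is mortality in the ICU (sections 3.1.1 and 11.1.1). Section 10, whose heading covers exclusion from analysis as well as drop-out, gives the drop-out criteria in 10.1. Item 2 reads "Serious adverse events occurred in patients or patients demands to be dropped out of the study due to adverse events" and item 4 reads "Severe hemorrhage".

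Section 11.3.1 defines the PP set: "The PP analysis is analysis including the data from patients who have successfully concluded the study protocol". It then ranks the analyses: "The data regarding validity is principally analyzed by PP analysis, and additionally analyzed by ITT analysis". Validity is this protocol's word for efficacy. The ITT set is limited to patients with confirmed vital status who, in the futhan arm, had at least one dose. It allows the last value to be carried forward "when there is a missing value or patient drop out before the study is over".

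Section 6.3.1 states: "We are planning to enroll 33 subjects per group that is suitable for inclusion/exclusion criteria and analyze final group of 31 subjects".

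Section 12.1(4) counts life-threatening circumstances and prolonged hospitalization as serious. Section 4.3 confirms that the trial is open label. Section 9.1, under general precautions, warns: "When used in extracorporeal circuit, this medication can aggravate hemorrhage".

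**The concern.** Put together, 10.1 and 11.3.1 describe a principal mortality analysis restricted to patients who finished the protocol, in which a severe bleed or any serious event counts as not finishing. A patient who bleeds severely on CRRT, is dropped, and later dies in the ICU could be missing from the primary result.

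Two things are at stake. First, if dropped patients die more often than the rest, the PP estimate that 11.2.1 checks against 50% is too low. Second, removal may differ between arms: one arm receives an anticoagulant that the protocol says can worsen bleeding, and staff who decide on drop-out know the assignment. The arm that loses more high-risk patients would look better, so a harm of the drug could turn into an apparent benefit.

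**Working it through.** **The plan's own figure.** Section 6.3.2 gives two-sided alpha = 0.10 (z = 1.645), p = 0.50, tolerance 0.15 and drop-out r = 0.05.

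- n = 1.645² × 0.5 × 0.5 / 0.15² = 30.06, rounded up to 31.
- 31 / 0.95 = 32.6, rounded up to 33.

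Both stated figures reproduce. The allowance is 33 − 31 = 2 patients per arm, or 2/33 = 0.06.

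**Effect of removal.** Let m = 0.50 be true ICU mortality (6.3.2), s the share of an arm dropped for a serious event or severe hemorrhage, and q their ICU mortality. The protocol gives neither s nor q, so both are varied.

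PP mortality = (m − s·q) / (1 − s); patients left per arm = 33 × (1 − s).

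| s | q = 50% | q = 60% | q = 70% | q = 90% | patients left |
|---|---|---|---|---|---|
| 0.05 | 50.0% | 49.5% | 48.9% | 47.9% | 31.35 |
| 0.10 | 50.0% | 48.9% | 47.8% | 45.6% | 29.7 |
| 0.20 | 50.0% | 47.5% | 45.0% | 40.0% | 26.4 |
| 0.30 | 50.0% | 45.7% | 41.4% | 32.9% | 23.1 |

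Two cells in full: s = 0.05 and q = 0.70 gives (0.50 − 0.035)/0.95 = 0.465/0.95 = 48.9%; s = 0.20 and q = 0.70 gives (0.50 − 0.14)/0.80 = 0.36/0.80 = 45.0%.

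**Effect on the comparison.** Take true mortality of 50% in both arms, s = 0.20 in one and s = 0.05 in the other:

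- q = 60%: 47.5 − 49.5 = −2.0 points
- q = 70%: 45.0 − 48.9 = −3.9 points
- q = 90%: 40.0 − 47.9 = −7.9 points

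The arm with more drop-outs appears to have the lower mortality although there is no true difference.

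**The case against.** The strongest reply is that the protocol never says outright that a patient with one of these events leaves PP.

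- Section 10.2, the explicit rule for disregarding data, lists missing consent, eligibility violations and prohibited medication, and neither of these events.
- The step from 33 to 31 is ordinary inflation and does not say which patients leave.
- A 5% allowance in hemodynamically unstable patients suggests that not every serious event was meant to remove someone.
- Section 10.1 opens with stopped medication as well as stopped observation, so drop-out might mean leaving treatment only.

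This stands to the extent that exclusion is an inference and the wording must be that patients may be removed. It does not dispose of the point: 10.2 deals with protocol violations and does not return 10.1 drop-outs to a set defined by completion.

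It is also fair that other analyses are planned. The additional ITT analysis and the 28-day Kaplan-Meier analysis on all subjects (11.3.3.2, item 6) should show a discrepancy, provided vital status is obtained after drop-out. Neither is the principal result, and the ITT set has its own restrictions and allows carry-forward.

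Two stronger readings are tempting and not supported.

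- A reader might infer that ICU deaths themselves drop out, because 12.1(4) lists death as serious. Section 8.3.3 and schedule footnote 2 treat death as a planned route to the closing examination, and 5% wastage beside 50% mortality makes sense only if deaths are kept.
- A reader might infer from 14.10 and the opening of 12.6 that any serious event halts the whole trial. Sections 8.3.3 and 10.1 (item 3) speak of the study being discontinued when they mean one patient's participation.

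**Conclusion.** The concern holds as a defect in what the protocol fixes: PP is principal for mortality, serious events and severe hemorrhage are drop-out criteria, and no text keeps those patients in PP. On the most natural reading, the primary result is conditioned on post-randomisation events that are likely to be tied to death.

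The size is uncertain. At the planned 5% drop-out and q = 70%, the bias is about 1 point, small beside the 15-point tolerance. It reaches 5 points at s = 0.20 and the same q, and the between-arm artefact is 2.0 to 7.9 points when s is 0.20 against 0.05. All of this rests on assumed s and q. There is no bias if q equals overall mortality, and the direction would reverse if q were below it. The protocol does not establish that removal will be unequal between arms; open-label conduct and the bleeding warning make it plausible.

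**What to change.** In 11.3.1, make the principal ICU-mortality analysis all randomised patients in the arm assigned, using observed vital status with no carry-forward for death, and make PP supportive. Promoting the present ITT set is not enough, because it leaves out futhan patients who were never dosed and patients without confirmed status, and allows the last value to be carried forward.

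In 10.1, state that a serious adverse event or severe hemorrhage stops assigned treatment only, and that ICU, hospital and 28-day vital status are still followed unless consent is withdrawn.

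The cost is a short amendment with IRB approval, plus continued chart follow-up of vital status for drop-outs. Sections 8.2.15 and 8.3.4 already plan mortality checks after CRRT, but do not say that they continue for patients who leave the study. Keeping all 33 per arm also improves precision slightly: the half-width at 50% mortality is 1.645 × √(0.25/33) = 14.3 points, against 1.645 × √(0.25/31) = 14.8 points with 31.

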## 10.2 Disposal of violation on protocol and non-compliance

The principal investigator and researchers should fully recognize and perform the study protocol, hence the protocol is not violated. However, the inevitable violation will be dealt with as follows.

In case of severe protocol violation, researcher should disregard the patient's data from the analysis and the criteria are as follows.

- ① Failure to acquire written consent
- ② Violation of inclusion/exclusion criteria
- ③ Administration of the medication that is prohibited to use in combination during the study.

Other violation of protocol that is decided to be minor and is not thought to influence the study analysis is thoroughly documented with the degree of violation, reason. Afterwards, the violation is evaluated by researcher, funder, monitor, statistician whether the violation has tempered with the study and included in the PP analysis.

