#### 4.3 Maintenance and revocation of double blind status

This study is open label clinical study, thus revocation is not required.

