#### 11.1.1 Primary validity assessment variable

Mortality at ICU

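### For violations judged minor, the researcher and the funder have a say in who stays in the principal (PP) efficacy set, and the protocol states no masking and no lock before mortality is tabulated

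*Protocol*

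**What the plan says.** Protocol section 10.2 sorts violations into two kinds.

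- **Severe.** Three categories are listed: no written consent, breach of the eligibility criteria, and use of a prohibited co-medication. The instruction is "In case of severe protocol violation, researcher should disregard the patient's data from the analysis and the criteria are as follows".
- **Other.** The next paragraph begins "Other violation of protocol that is decided to be minor and is not thought to influence the study analysis is thoroughly documented", with its degree and reason. It ends "Afterwards, the violation is evaluated by researcher, funder, monitor, statistician whether the violation has tempered with the study and included in the PP analysis".

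Section 11.3.1 defines the set only in general terms: "The PP analysis is analysis including the data from patients who have successfully concluded the study protocol". It then ranks the analyses: "The data regarding validity is principally analyzed by PP analysis, and additionally analyzed by ITT analysis".

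The primary variable in section 11.1.1 is "Mortality at ICU". On blinding, section 4.3 says "This study is open label clinical study, thus revocation is not required".

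**The concern.** A per-protocol set is credible when membership follows from rules, or from a review that cannot see the result. Section 10.2 instead names a four-member panel that includes the treating side and the funder, and asks it whether a violation affected the study. In an open-label ICU trial the researcher knows which arm the patient was in and whether the patient died. The protocol does not say that this information is kept from the other three members, or that the decision is closed before deaths are counted by group.

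The earlier step is also a judgement. Section 10.2 gives no list of minor violations and does not say who decides that a violation is minor.

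What is at stake is the denominator of the principal mortality comparison. This differs from the question of whether PP should be the principal set at all. Even a supportive PP analysis is weakened if its membership can respond to the outcome.

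**Working it through.** **1. The protocol's own figure.** Section 6.3.2 gives α = 0.1, p = 0.50, δ = 0.15 and a loss of 5%.

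- n = Z²p(1−p)/δ² = 1.645² × 0.25 / 0.0225 = 30.06, rounded up to 31.
- 31 / 0.95 = 32.6, rounded up to 33.

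The stated 31 analysed and 33 enrolled per group reproduce. The planned loss is 33 − 31 = 2 patients per arm, which gives a scale for the number of exclusions to consider.

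**2. What the text leaves to discretion.**

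| Step in section 10.2 | Who acts | Criterion stated | Masking or timing stated |
|---|---|---|---|
| Remove severe cases | researcher | three listed categories | none |
| Call a violation minor | not named | judgement | none |
| Decide PP inclusion for a minor violation | researcher, funder, monitor, statistician | whether it affected the study | only that it comes after documentation |

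Patients with no violation are not touched by the panel.

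**3. Illustration of sensitivity.** The protocol gives no number for such exclusions, so the following are assumptions: 33 randomised per arm, true mortality of 50% in both arms, a pooled z test, and exclusions always in the direction that favours futhan. The level is two-sided 0.1. The protocol uses that level in its sample-size formula and gives none for the group comparison.

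With a futhan deaths and b control deaths, each Binomial(33, 0.5), remove k₁ futhan deaths and k₂ control survivors. Then

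z = (b/n₂ − (a−k₁)/n₁) / √[p̄(1−p̄)(1/n₁ + 1/n₂)], with n₁ = 33 − k₁, n₂ = 33 − k₂ and p̄ the pooled proportion of deaths after the exclusions.

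Summing the exact probabilities of all (a, b) with z > 1.645 gives the chance of a false result favouring futhan. Using |z| > 1.645 gives the two-sided rate.

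| Futhan deaths removed | Control survivors removed | Significant, favouring futhan | Significant, either direction |
|---|---|---|---|
| 0 | 0 | 5.4% | 10.9% |
| 1 | 0 | 6.0% | 9.4% |
| 2 | 0 | 8.8% | 12.0% |
| 1 | 1 | 8.8% | 12.0% |
| 2 | 2 | 13.4% | 15.2% |

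The two-sided rate moves little when exclusions come from one arm, because gains in one tail are offset by losses in the other; the dip at one exclusion reflects discreteness. The rate favouring futhan is the relevant measure, since the worry is about exclusions in one direction. At a two-sided level of 0.05 the corresponding chances are 3.2% with none removed, 5.5% with two futhan deaths removed, and 8.8% with two removed from each arm.

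**4. The same point with assumed counts.**

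- 13/33 against 20/33 deaths: z = 1.72, p = 0.085.
- After dropping two futhan deaths and two control survivors, 11/31 against 20/31: z = 2.29, p = 0.022.

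**The case against.** Several objections stand and limit the point.

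- **Scope.** A reader might infer that the funder and the researcher choose the analysed patients. The text does not support that. Three categories are excluded by written rule, the panel rules only on other violations judged minor, and the monitor and statistician are half of it.
- **Silence.** A reader might infer that there is no masking. The protocol only states none. A statistical analysis plan, not shown here, could add a masked review and a lock. Nor does the text place the review after outcomes are tabulated; it places it after documentation. Even so, the make-up of the panel is fixed in the protocol. A later plan that took the decision away from the researcher and funder would contradict section 10.2, so the sentence needs changing there.
- **Safeguards.** An ITT analysis is also required, and violations must be recorded with degree and reason. Both help. However, ITT is ranked as additional, so the headline result still comes from the set that is open to discretion. Death is an objective outcome, but that protects how it is recorded, not who is counted.
- **Size.** The illustration is worst-case. The 13.4% needs four exclusions, all in the favourable direction, and nothing in the protocol suggests that this was planned or happened. It may also be tempting to set a shift in the group difference against the 15-point tolerance. Section 6.3.2 defines that tolerance as the precision for estimating mortality in the futhan group, so it is no yardstick for a difference.
- **Other discretion.** Section 10.1 also allows drop-out "When the patient is decided not fit for the study progression by researchers". That is a separate route, and changing the panel alone would not close it.

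**Conclusion.** The point holds in this limited form: for violations outside the severe list and judged minor, people who know arm and outcome have a say in membership of the principal efficacy set, and the protocol states neither masking nor a lock. The conclusion rests on the wording of section 10.2 together with the open-label design and the ranking of PP above ITT. It does not rest on any evidence of misuse.

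Under the stated assumptions, exclusions within the planned loss of two per arm can raise the chance of a false result favouring futhan from 5.4% to 8.8% if they come from the futhan arm only, and to 13.4% if they come from both. These figures show how few decisions matter in a trial of this size; they do not predict the bias. The point is a cheap improvement.

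**What to change.** Replace the last part of section 10.2 with wording to this effect:

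> Each violation is classified as severe or minor, and PP membership is decided, by written criteria from a listing that shows neither treatment group nor vital status. Both decisions are signed and locked before mortality is tabulated by group. Researchers and the funder supply facts about the violation but do not decide. Violations that reveal the treatment group are handled by a criterion fixed in advance.

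Three details matter.

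- The change must cover the sorting into severe and minor as well as the final inclusion, because both steps affect the set.
- Only one arm receives an infusion, so some violations will show the arm whatever the listing hides. The advance criterion for these has to be written, not just promised.
- The protocol should name who decides. Section 14.7 says that monitoring is contracted out by the funder, so a decision by the monitor would not be fully separate from it. The written criteria, the masked listing and the lock should carry the protection.

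The cost is a rewritten paragraph, a short list of criteria and a small amount of data-management work for the listing. The sample size does not change.
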